**Figure 2 figure2:**
[figure not shown]
Study design flow diagram.

World Health Organization trial registration data set.
**Trial registration data set**
Primary registry and trial identifying number: German Clinical Trials Register DRKS00018078Date of registration in primary registry: October 2, 2019Secondary identifying numbers: noneSource of monetary or material support: Boehringer Ingelheim FoundationPrimary sponsor: Boehringer Ingelheim FoundationSecondary sponsor(s): not applicableContact of public queries: [contact] (DO); [contact] (AB)Contact for scientific queries: [contact] (AB)Public title: mediators of a link between innate or acquired aerobic capacity and stress resilienceScientific title: The association of innate and acquired aerobic capacity with resilience in healthy adults: Protocol for an 8-week randomized controlled, web-based, physical exercise intervention studyCountries of recruitment: GermanyHealth condition(s) or problem(s) studied: healthy participantsIntervention(s): web-based exercise intervention; controlKey inclusion criteria:Age: 18-45 yearsHealthySuitable for sportsPhysically inactive (<150 minutes/week physically active)Gender: male and femaleKey exclusion criteria:Absolute contraindications to exerciseSmoker or other tobacco consumptionHigh blood pressureLong-term medication intakeHairless participants (<1 cm)Shift workerParticipation in another studyPsychological disordersStudy type:InterventionalAllocation: randomized, controlledIntervention model: parallel assignmentPrimary purpose: preventionDate of first enrollment: September 10, 2019Target sample size: 70Recruitment status: RecruitingPrimary outcome(s):Improvement of the maximum oxygen uptake through an 8-week web-based training intervention.Investigation of the link between the changes in maximum oxygen uptake induced during training intervention and the associated changes in salivary cortisol induced during a stress test.Key secondary outcomes:Investigation of the link between maximum oxygen uptake and resilience by determining physiological and biochemical markers in the untrained state before an 8-week web-based training intervention.Investigation of the link between the changes in maximum oxygen uptake and resilience induced through training intervention by determining physiological and biochemical markers.Sustainability of the change in resilience 12 and 24 weeks after 8 weeks of web-based training intervention.

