### Objectives

In this study, we implement an 8-week randomized controlled trial of a web-based, individualized physical exercise training intervention to evaluate the link between aerobic capacity and resilience in healthy untrained adults. Therefore, baseline values of performance diagnostics to determine the innate aerobic capacity (VO_2_peak) as well as emotion regulation abilities, stress reactivity, and stress recovery (saliva cortisol) as potential resilience mechanisms are estimated. We hypothesize that (1) participants with a high innate aerobic capacity will show a higher resilience to stress compared with participants with low aerobic capacity. This will be followed by 8 weeks of individualized web-based physical exercise training combining continuous and interval-type running exercises with the aim of progressively increasing aerobic capacity. After completion of the exercise intervention, performance diagnostics will be repeated to estimate the acquired aerobic capacity, as well as to assess the psychological parameter. In addition, secondary outcomes of molecular factors, including hair cortisol levels, endocannabinoids, catecholamines, cytokines, and cell-free DNA, and results of several questionnaires will be determined throughout the study. We hypothesize that (2) the exercise intervention will improve the aerobic capacity of the intervention group, which (3) will be accompanied by improvements in resilience factors. This will offer the possibility to exploratively study the underlying molecular mechanism (stress hormone release and immune reactions) in the promotion of resilience by regular physical activity.

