**Figure 1 figure1:**
[figure not shown]
SPIRIT (Standard Protocol Items: Recommendations for Interventional Trials) diagram of enrollment, interventions, and assessments. ADS: Allgemeine Depressionsskala; ASI: Anxiety Sensitivity Index; BRS: Brief Resilience Scale; BSI: Brief Symptom Index; CERQ: Cognitive Emotion Regulation Questionnaire; CG: Control Group; CTQ: Childhood Trauma Questionnaire; ECG: electrocardiogram; ERQ: Emotion Regulation Questionnaire; GOT: Glutamate Oxalacetate Transaminase; GPT: Glutamate Pyruvate Transaminase; GSE: General Self-Efficacy Scale; HPA: Habitual Physical Activity Questionnaire; IG: Intervention Group; IPAQ: International Physical Activity Questionnaire; MDBF: Mehrdimensionaler Befindlichkeitsfragebogen; PAR-Q: Physical Activity Readiness Questionnaire; PSS-10: Perceived Stress Scale–10; SCS-D: Self-compassion Scale–German Version; SECPT: socially evaluated cold pressor test; SF-36: Short-Form Health Survey; SRS: Stress Reactivity Scale; TICS-SSCS: Trier Inventory for the assessment of Chronic Stress–Screening Scale For Chronic Stress.

The primary (VO_2_peak and saliva cortisol) and key secondary outcomes, trial methods, and designs are summarized in the World Health Organization trial registration data set (Textbox 1). This study includes 4 time points of investigation of physiological and psychological parameters, including the primary end points of a change in VO_2_peak and saliva cortisol from the baseline: at T0 and T1, baseline values will be estimated, and at T2 and T3, data collection following the control or exercise intervention will be performed. T0 and T2, as well as T1 and T3, are structured in the same way, except for the separately listed psychological examinations at the measurement points. T1 and T3 will be performed after a maximum of 10 days after T0 and T2, respectively. Written consent after a detailed oral explanation will be obtained from all participants at the beginning and after completion of the study by the responsible study physician. At the beginning of the study (T0), the participants will not be fully informed about the purpose and aim of the psychological stress tests. Full clarification will take place at T3. If a participant wishes to discontinue the study prematurely, they will be fully informed about the purpose and aim of the psychological stress tests.

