### Statistical Methods

The power calculation was based on the analyses of the primary outcomes, that is, aerobic capacity (VO_2_peak) and experimental stress reactivity (saliva cortisol). On the basis of the results of Bacon et al [122], the sample size was determined a priori via power analysis (G*Power V5), yielding a minimum sample size of 67 for a medium-to-large effect size of *f(V)*=0.35. An alpha error set to .05 and statistical power of 0.80 were assumed for a multivariate analysis of variance (MANOVA) with 2 repeated measurements, 2 groups, and interaction effects. Descriptive statistics will be used for all outcome measures at each time point to give an overview of all results. First, MANOVA will be performed with the main primary outcomes as dependent variables, that is, aerobic capacity (VO_2_peak) and experimental stress reactivity (saliva cortisol) to maximize the power of the analyses and to be able to investigate the main and interaction effects of time (baseline [T0, T1] vs post [T2, T3]) and group (IG vs CG). Groups should be equal at preintervention (T0 and T1). A time effect should be observed for the IG. Furthermore, we expect a significant time×group interaction as the IG should react differently over time, with a higher increase in aerobic capacity (VO_2_peak). Significant effects of the MANOVA will be followed up by posthoc analyses of variance. As a secondary aim of our study, we aim to identify variables (eg, emotion regulation and biological metrics) that mediate the relationship between physical exercise and resilience outcomes. To that end, we plan to calculate multiple regression analyses that include potential mediators. Principal component analyses regarding potential mediating variables will precede the mediator analyses to avoid redundancy in our regression models. This will be statistically detailed with posthoc tests and corrections for multiple comparisons (Bonferroni-Holm correction [123]). Missing data will be omitted from the data set.

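### The registered second primary outcome is a link between two changes, but the planned and powered primary analysis compares group means and does not estimate that link

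*Protocol article*

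**What the plan says.** Three places in the protocol article define or analyse the primary outcomes, and they do not agree.

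- **Trial registration data set (Textbox 1).** The first primary outcome is "Improvement of the maximum oxygen uptake through an 8-week web-based training intervention". The second is "Investigation of the link between the changes in maximum oxygen uptake induced during training intervention and the associated changes in salivary cortisol" during a stress test.
- **Trial Design and Participants, after Figure 1.** The text refers to "the primary end points of a change in VO_2_peak and saliva cortisol from the baseline". These are two separate changes, and no link is mentioned.
- **Statistical Methods.** "MANOVA will be performed with the main primary outcomes as dependent variables, that is, aerobic capacity (VO_2_peak) and experimental stress reactivity (saliva cortisol"), with the purpose "to investigate the main and interaction effects of time (baseline [T0, T1] vs post [T2, T3]) and group (IG vs CG"). Significant effects lead to post hoc analyses of variance. The sample size of 67 is derived for this MANOVA.

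The only association-type analysis in Statistical Methods is multiple regression with potential mediators. It is presented as a secondary aim, concerns variables lying between exercise and resilience outcomes, and is not tied to the second primary outcome.

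Strengths and Limitations adds that the two stress tests (cold pressor at T0, ScanSTRESS at T2) give measures that are not directly comparable, and that the design does not permit within-subject analyses.

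**The concern.** A link between two changes and a difference in group means are different quantities. The time-by-group MANOVA asks whether the arms differ in their mean vector of VO2peak and cortisol. It can be significant because of VO2peak alone, and it does not use the covariation of the two changes as an estimate or a test of anything. One of the two registered primary outcomes therefore has no planned analysis that answers it, and the power calculation does not cover it.

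The registered wording is the public commitment against which the result will be judged. As the plan stands, the trial could report a significant primary result while its registered question about fitness and stress reactivity stays unanswered. It could equally report a null MANOVA although a link exists.

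**Working it through.** **1. Reproduce the stated sample size, to see what it covers.** Inputs from Statistical Methods: f(V)=0.35, alpha 0.05, power 0.80, 2 groups, 2 measurements. For the within-between interaction, df1 = (2−1)(2−1) = 1, df2 = N−2 and λ = f² × N.

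- At N=67, λ = 0.1225 × 67 = 8.21 and power is 0.806; N=66 gives just under 0.80. The protocol's 67 is reproduced.
- This is a contrast of mean changes between arms. It says nothing about power for an association.

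**2. How often is the omnibus test significant when there is no link?** Assumptions: VO2peak change differs by d between arms, cortisol has no group effect, and the two changes are uncorrelated. With two groups d = 2f, so the planned 0.35 corresponds to d=0.7. N=62 is the target of 70 less the 11.4% dropout in Results: 70 × 0.886 = 62.0. For the joint test of two changes with n per arm, F has 2 and 2n−3 degrees of freedom and λ = (n/2) × d².

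| d (VO2peak) | λ at N=62 (15.5 × d²) | MANOVA significant, N=62 |
|---|---|---|
| 0.5 | 3.88 | 39% |
| 0.7 | 7.60 | 67% |
| 1.0 | 15.5 | 94% |
| 1.2 | 22.3 | 99% |

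At N=70 and d=0.7, λ = 17.5 × 0.49 = 8.58, and the MANOVA is significant in 73%.

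**3. Simulation of the omnibus test beside a direct test of the link** (20,000 runs, 35 per arm; the link is tested as the pooled within-group correlation of the two changes):

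| Scenario | MANOVA significant | Correlation test significant |
|---|---|---|
| VO2peak d=0.7, cortisol 0, correlation 0 | 72.8% | 5.0% |
| No mean differences, correlation −0.5 | 5.1% | 99.4% |
| Both means shift by d=0.7, correlation 0 | 96.2% | 5.0% |

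The MANOVA can be positive without a link and negative with a strong one.

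**4. Does the follow-up step contain the problem?** In simulation of the planned sequence (31 per arm, no cortisol effect, uncorrelated outcomes), the MANOVA and the cortisol ANOVA were both significant in about 4% to 5% of runs for d from 0.5 to 1.2. The follow-up guards against claiming a cortisol effect that is not there. It is still a comparison of means.

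**5. What could the trial detect if the link were tested?** The documents give no expected correlation. By Fisher z (two-sided 0.05, power 0.80), the smallest detectable simple correlation is tanh[(1.960 + 0.842)/√(n−3)]:

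- n=70: 0.33
- n=62: 0.35
- trained arm only, n=35: 0.46
- trained arm only, n=31: 0.48

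The total n needed for other assumed values is 194 (r=0.2), 85 (r=0.3), 47 (r=0.4) and 30 (r=0.5).

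**6. Can the registered quantity be formed?** The registered link needs a cortisol change per person. The protocol's own account of its two stress tests rules out within-subject analysis, so a T2-minus-T0 score is not a sound basis for it.

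**The case against.** - **The plan already tests cortisol on its own.** This stands. A reader might infer from the omnibus rates that a false claim about stress reactivity is likely. The documents do not support that, because the post hoc cortisol ANOVA holds such a claim near 5%. A figure of 99% also needs d=1.2, which appears nowhere in the protocol; the planned effect size corresponds to 67% at N=62.
- **The link may be meant at group level.** The objectives expect training to raise capacity and resilience to improve alongside it. On that reading, a time-by-group test with both follow-up ANOVAs is relevant, and the registered wording does not exclude it. But two means moving together is compatible with a link without establishing one (third scenario in the simulation), and the registry and the Methods would still name different primary outcomes.
- **The mediator regressions could be adapted.** They could, but they are labelled secondary, are not specified as relating cortisol to VO2peak change, and are not powered.
- **Detail may sit in the full protocol or analysis plan.** That would answer a missing model. It does not answer a conflict between statements in one article, one of which fixes and powers the primary analysis. It does cover the first hypothesis, on baseline capacity and resilience. A reader might infer that this too is a primary question left untested, but the baseline link is registered as a key secondary outcome, and an article may leave its model to the fuller document.

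**Conclusion.** The mismatch is real: registry entry, Methods wording and primary analysis name two different quantities for primary outcome 2, and no planned primary analysis estimates the registered one. The omnibus MANOVA is uninformative about the link. It is significant in about 67% (N=62) to 73% (N=70) of trials with no link at an assumed d=0.7, in 39% to 99% at N=62 for d from 0.5 to 1.2, and in about 5% when a within-group correlation of −0.5 exists without mean differences. These rates assume normal changes and, for the no-link cases, uncorrelated outcomes.

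It does not follow that the trial lacks a valid test of cortisol or that its randomised comparisons fail: both outcomes keep separate between-arm tests. The defect is confined to what the trial may conclude about the fitness–cortisol link.

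**What to change.** Use one definition in the registration data set, Trial Design and Participants, and Statistical Methods:

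1. **Primary outcome 2:** the between-group difference in T2 cortisol reactivity, with T0 reactivity as a covariate and no change score. A covariate need not be on the same scale as the outcome, so this is consistent with the protocol's statement about its two stress tests.
2. **Interpretation:** state that a significant omnibus MANOVA alone is not evidence of a fitness–resilience link.
3. **The link as a secondary outcome:** regress T2 reactivity on VO2peak change (T3 minus T1), adjusted for T0 reactivity, gender and BMI stratum. Report it with and without group. Including group removes the randomised between-arm difference in fitness; leaving it out mixes that difference with differences between individuals. Label both as observational associations.
4. **If the link stays primary:** name that regression as the primary analysis and state its precision. The detectable simple correlations are about 0.33 (N=70), 0.35 (N=62) and 0.46 to 0.48 (trained arm alone, n=35 to 31). They serve as a guide only, because they do not describe the group-adjusted model.
5. **Registry:** update the entry and report the change.

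The cost is wording in three places, a registry update, and one or two regressions on data already being collected. Results reports 31 completers with recruitment paused, so this can be settled before the trial is complete.

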### Randomization

The included participants will be randomly assigned with a 50%-50% allocation to the IG or CG. Randomization will be performed using the EXCEPT NUMBER command in Microsoft Excel. In addition, randomization will be stratified by gender with an expected ratio of 50%-50% and BMI with an expected ratio of 33% overweight (BMI ≥25) and 67% normal weight (BMI <25) to recruit CG and IG participants with homogeneous baseline characteristics.

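### The primary MANOVA omits the gender and BMI strata and compares change scores; adjusting post values for baseline and strata is at least as efficient in large samples and suits cortisol better

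*Protocol article*

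**What the plan says.** The Randomization section has participants "randomly assigned with a 50%-50% allocation to the IG or CG". It adds that "randomization will be stratified by gender with an expected ratio of 50%-50% and BMI with an expected ratio of 33% overweight", the BMI cut being 25, and gives the purpose as "to recruit CG and IG participants with homogeneous baseline characteristics".

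In Statistical Methods, "MANOVA will be performed with the main primary outcomes as dependent variables". These outcomes are VO2peak and saliva cortisol, and the effects examined are the "main and interaction effects of time (baseline [T0, T1] vs post [T2, T3]) and group (IG vs CG"). On the result that matters, "we expect a significant time×group interaction as the IG should react differently over time". Significant effects are followed by post hoc ANOVAs. Neither gender nor BMI, nor a baseline covariate, is named in the model or in the power calculation, which is for two groups and two repeated measurements.

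The two stress tests differ: the cold pressor test at T0 and the compact ScanSTRESS task at T2. Strengths and Limitations says their measures cannot be compared directly and that within-subject analysis is therefore ruled out. It also says that differences before the intervention are accounted for by the T0 test.

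**The concern.** When allocation is balanced on a factor that predicts the analysed quantity, the estimated group difference is already protected against imbalance in that factor. A model without the factor still counts its variance as error. The reported standard error is then too large, and the test rejects less often than its nominal level.

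The second part concerns the baseline. With two time points, the time×group interaction subtracts each participant's baseline from the post value. For VO2peak this is valid, though not the most efficient use of the baseline. For cortisol it subtracts the response to one stressor from the response to a different one, which conflicts with the article's own statement about comparability.

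At stake is avoidable imprecision in a small trial, and a cortisol analysis that does not match the limitation the article itself declares.

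**Working it through.** **Inputs from the protocol.** f(V) = 0.35, alpha 0.05, power 0.80 and minimum N 67 (Statistical Methods); target 70 (trial registration data set); dropout 11.4% (Results).

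**Assumed, not in the protocol.** R², the share of variance in change explained by gender and BMI; ρ, the correlation between baseline and post value.

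**1. The plan's own figure.** For the interaction with 2 groups and 2 times, take a noncentral F with λ = N·f² and 1 and N−2 degrees of freedom. f² = 0.1225.
- N = 66: power 0.7997.
- N = 67: λ = 67 × 0.1225 = 8.21, power 0.8058.

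The smallest N reaching 0.80 is 67, so the stated figure reproduces exactly. It belongs to a one-outcome model without covariates.

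**2. What the interaction tests.** It compares D = post − pre between groups. An effect of gender or BMI on the level of an outcome enters both terms and cancels. Only an effect on D stays in the error.

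**3. Adding gender and BMI.** λ = N·f²/(1−R²), with 1 and N−4 degrees of freedom; the standard error ratio (adjusted to unadjusted) is √(1−R²). If 70 are enrolled, 70 × (1 − 0.114) ≈ 62 complete.

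| R² of change | SE ratio | Power at 62 | Power at 67 |
|---|---|---|---|
| no adjustment | – | 0.774 | 0.806 |
| 0 | 1.00 | 0.773 | 0.805 |
| 0.05 | 0.975 | 0.794 | 0.825 |
| 0.10 | 0.949 | 0.815 | 0.845 |
| 0.20 | 0.894 | 0.858 | 0.884 |

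**4. Simulation with stratified allocation.** N = 68, 6,000 runs per scenario, ρ = 0.8, effect 0.7 SD of change (2 × 0.35), strata explaining 0% or 50% of level.

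| R² of change | Type I error, unadjusted | Power, unadjusted | Power, adjusted |
|---|---|---|---|
| 0 | 0.048–0.052 | 0.813–0.818 | 0.812–0.813 |
| 0.10 | 0.034–0.040 | 0.819–0.824 | 0.844–0.850 |
| 0.20 | 0.028–0.030 | 0.837–0.840 | 0.889–0.892 |

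With strata explaining 50% of level and none of change, power is 0.818 unadjusted and 0.813 adjusted, so nothing is lost. When the strata do predict change, the unadjusted test is conservative. Its power also rises somewhat, because stratified allocation already balances the factors. The gain from adjustment is therefore about 0.03 at R² = 0.10 and 0.05 at 0.20, smaller than the table in step 3 suggests.

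**5. Change score against baseline adjustment.** Write σ₀ and σ₁ for the SDs of the baseline and post values.
- Variance of change: σ₀² + σ₁² − 2ρσ₀σ₁.
- Residual variance after adjustment: σ₁²(1−ρ²).
- Difference: (σ₀ − ρσ₁)², which is never negative.

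With equal variances the ratio of adjusted to change is (1−ρ²)/(2(1−ρ)) = (1+ρ)/2:
- ρ = 0.9: 0.95
- ρ = 0.8: 0.90
- ρ = 0.3: 0.65

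**6. Cortisol.** Statistical Methods enters cortisol with a time factor, T0 against T2. Strengths and Limitations says those two measurements are not comparable. A regression of the T2 response on the T0 response needs no common scale, and it is a direct way to account for differences before the intervention. Once the T2 response itself is the outcome, effects of gender or BMI on its level no longer cancel, so the case for strata terms is stronger there than for the VO2peak interaction.

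**The case against.** The strongest reply is that nothing is shown to be lost. The planned effect is an interaction, effects on level cancel, and the protocol nowhere says that gender or BMI predicts change. This stands. A reader might infer that a model without the strata necessarily loses precision, but at R² = 0 the gain is nil.

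A reader might also infer that the omission biases the comparison or undermines the planned 80% power. It does neither. The unadjusted test is at worst conservative, and the 67 was calculated without covariates. Nor does the figure of 62 prove a shortfall, since the article does not say whether 70 counts enrolled participants or completers.

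The 35% reduction for cortisol at ρ = 0.3 should not be presented as an expected gain. Both ρ and equal variances are assumed, and the comparator is a change score between unlike tests.

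A further reply is that the article is condensed and the full plan may list covariates. It may, but the article does name the effects of its primary model, and the time factor for cortisol conflicts with its own limitation whatever the covariate list says.

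Finally, two separate primary ANCOVAs would replace the single multivariate test and raise a multiplicity question. That is fair, and it is met by keeping the multivariate test first.

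**Conclusion.** The point holds in a limited form. Allocation is stratified by gender and BMI, and the stated primary model has neither. Omitting them introduces no bias, but makes the test conservative and may cost precision if they predict the change in VO2peak or the T2 cortisol response. At about 62 completers, power moves from 0.774 to between 0.773 and about 0.86 over an assumed R² of 0–20%. The upper part of that range is somewhat generous, because the unadjusted test also gains from stratified allocation. In simulation at N = 68, unadjusted type I error is about 0.03–0.04 when the strata explain 10–20% of change.

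Baseline adjustment is the stronger half. In large samples it is never less efficient than the change score, and for cortisol it avoids subtracting responses to two different stressors.

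These results rest on assumed R² and ρ, on allocation being balanced within the four gender-by-BMI cells, and on calculations for one outcome at a time. The point is a worthwhile improvement at little cost and does not invalidate the trial.

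**What to change.** In Statistical Methods, keep the multivariate test as the first step, but apply it to the post values: VO2peak at T3 and cortisol reactivity at T2. Its terms are group, the two baseline values (VO2peak at T1, cortisol reactivity at T0), gender and BMI stratum. Follow it with one ANCOVA per endpoint on group, that endpoint's own baseline, gender and BMI stratum, and report the adjusted group difference with its 95% CI. Align the text with Strengths and Limitations, so that cortisol is no longer analysed as a T0-to-T2 time effect.

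The cost is 3 degrees of freedom in each ANCOVA and 4 in the multivariate model, out of about 60. The power basis must also be restated, because 67 belongs to a one-outcome interaction without covariates. The change should be fixed before the data are analysed.
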